## **12.2 Audits**

The QA department of sponsor (or the third party) will perform audits for the study centres.

The auditor will perform systemic auditing for the activities and documents related to clinical study to assess whether the study comply with the protocol, SOP and other related regulations; whether the data is recorded truly, accurately, completely and without delay. The audits should be performed by the personnel unrelated to the clinical study.

## **12.3 Inspections**

The authorities might perform inspections during or after the clinical study. As soon as the investigator is notified of a planned inspection by the authorities, he will inform the sponsor immediately. Sponsor will help and coordinate study centres to participate the inspection by authorities.

For the purpose of ensuring compliance with the Clinical Trial Protocol and applicable regulatory requirements, the investigator should permit auditing by or on the behalf of the sponsor and inspection by regulatory authorities. The investigator agrees to allow the auditors/inspectors to have direct access to his/her study records for review, being understood that these personnel is bound by professional secrecy, and as such will not disclose any personal identity or personal medical information.

The investigator will make every effort to help with the performance of the audits and inspections, giving access to all necessary facilities, data, and documents. As soon as the investigator is notified of a planned inspection by the authorities, he will inform the sponsor and authorize the sponsor to participate in this inspection. Any result and information arising from the inspections by the regulatory authorities will be immediately communicated by the investigator to the sponsor. The investigator shall take appropriate measures required by the sponsor to take corrective actions for all problems found during the audit or inspections.

## **APPENDIX C:**

### **Samples collection, transport and test results report procedures**

#### **(For Study 2015BAI12B13)**

## **1. Sample Collection**

### **1) Materials**

1.1 Self-prepared: 5ml gel and vacuum blood collection tubes, 2ml and 5ml EDTA anticoagulated vacuum blood collection tubes, 2ml or 5ml sodium fluoride anticoagulated vacuum blood collection tubes, disposable venous blood collection needles, cuff, curved plate, skin disinfectant (75% alcohol or iodine) and sterilized cotton swab, etc.

1.2 Provided by center laboratory: Serum collection tubes, disposable blank label, small-sized sealing bags, large-sized sealing bags, disposable sterile Pasteur pipette, marking pen.

### **2) Test items**

2.1 Items tested by each center: 0min, 60min, 120min blood glucose, HbA1c, blood routine, liver and kidney function, serum lipids, electrolytes, 24-hour urinary electrolytes (calcium and phosphorus), urinary albumin creatinine ratio.

2.2 Items tested by center laboratory:

- a. GADA (sample should be collected under fasting status);
- b. 25 (OH) D (sample should be collected under fasting status);

c. 0min, 60min, 120min C-peptide;

d. Genetic testing (for further research on HLA-DQ, DR, vitamin D receptor gene polymorphism and immune repertoire diversity, currently results of this part will not be provided).

### **3) Sample numbering and labeling**

3.1 Screening numbering of subjects: L2-XX-YYY;

Notation: L2-fixed format, XX is the number of the center, YYY is the number of the subject (numbered sequentially according to the screening order);

Example: L2-20-001, “20” is the center numbered 20, “001” is the first subject during screening.

3.2 Sample numbering: screening number of the subject + V□ + a/c/d

Constitution: Screening number + times of visit + time points of blood collection should fill in the number of visits; a, c, d represents the time points of blood collection, which is 0min, 60min and 120min respectively.

Example of sample numbering: L2-20-001V5a, “L2-20-001” is the screening number, “V5a” is the 0min (fasting) sample of the 5th visit; similarly, the 60min postprandial sample of the 30th visit of the same subject should be L2-20-001V30c.

Labeling requirements (items tested by center laboratory): names, sample number of the subject should be written clearly on a blank label sticker and posted on the relevant serum collection tube.

### **4) Sample distribution and storage of center lab tested items**

#### **4.1 Fasting serum samples (GADA, 25 (OH) D, fasting C-peptide):**

- Prepare one 5ml gel and vacuum blood collection tube;
- Collect 5ml fasting venous blood;
- Centrifuge at 2000g (approximately 3000 rpm / min) for 5 minutes to separate the serum within 2h;
- Use disposable sterilized Pasteur pipette and carefully transfer the serum into serum collection tube(s) with written label(s), confirm the lid is covered.

#### **4.2 Fasting blood samples for further genetic research:**

- Prepare 5ml EDTA anticoagulant tube, paste written label;
- Collect 3ml fasting venous blood;
- Immediately mix by inversion for more than 10 times.

#### **4.3 60min, 120min postprandial C-peptide sample:**

- Prepare 5ml gel and vacuum blood collection tube;
- 60min, 120min postprandial should each collect 5ml venous blood;
- Centrifuge at 2000g (approximately 3000 rpm / min) for 5 minutes to separate the serum within 2h;
- Use disposable sterilized Pasteur pipette and carefully transfer the serum into serum collection tube(s) with written label(s), confirm the lid is covered.

#### **4.4 Storage:**

- Specimens should be stored under -20 °C within 2h;
- If samples cannot be stored under -20 °C timely, then it should be stored at 4 °C temporarily (not more than 4h).

## **2. Transportation**

- 1) Place the labeled serum collection tubes into relevant small-sized sealing bags, sealed.
- 2) Blood samples should all be put in a large-sized sealing bag while transportation to center laboratory each time, a printed list of names and sample numbers should be attached in the sealed bag, information of hospital and time of submission should be written on the large-sized sealed bag.
- 3) Deliver samples using dry ice to center laboratory every 14 days (refer to clinical sample transport operating instructions).

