The research team conducted a preliminary experiment in the early stage, including 10 normal volunteers with normal glucose tolerance, taking oral vitamin D3 2000 IU/day for 3 months. At the beginning of the study and at the 2nd, 4th, 8th and 12th week of the

study, 25(OH)D levels, serum calcium and phosphorus levels, and 24-hour urinary calcium and phosphorus excretion were monitored. The 25(OH)D level of all volunteers was within the safe range ( $<500$  nmol/L), and there was no abnormality in serum calcium and phosphorus levels and 24-hour urinary calcium and phosphorus excretion.

Therefore, combined with domestic and foreign guidelines, existing research and our pre-experiments, it is concluded that vitamin D3 2000 UI/d is a safe dose and the possibility of poisoning is low. To ensure the safety of the study and detect vitamin D3 excessive promptly, we will measure vitamin D3 levels, serum calcium, phosphorus, 24-hour urinary calcium and phosphorus, and monitor urinary ultrasound before randomization and at 4, 12, 26, 52, 78 and 104 weeks after intervention. According to China's Vitamin D and Adult Skeletal Health Guidelines, which cited the United States guidelines, a potential vitamin D poisoning should be considered when 25(OH)D level persistently over 500 nmol/L. In this study, when 25(OH)D $>250$  nmol/L, the supplemental dose of vitamin D needs to be reduced to 800 IU/day. If patient develops hypercalcemia, physicians should look for possible causes, such as dehydration (most likely), mild primary hyperparathyroidism, high calcium intake, infection, etc., and provide treatment accordingly.

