### **7.2.1 Laboratory tests**

The sponsor will assign the central laboratory to carry out the safety assessment: test of 25(OH)D. Other clinical lab tests will be carried out at laboratories of each research center.

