## 8.6 Treat on hypercalcemia

Clinical manifestations of hypercalcemia are associated with the magnitude and speed of the increase of serum calcium. Mild hypercalcemia may be asymptomatic. symptoms include anorexia, nausea, vomiting, constipation, fatigue, muscle fatigue, reduce of muscle tension, polydipsia, polyuria; drowsiness, confusion, and even coma. ECG may show shortening of Q-T interval, the change of ST-T, atrioventricular block and hypokalemic u waves. If not treated timely, it may result in fatal arrhythmia. Long duration of hypercalcemia can lead to calcium deposition within various tissue and organ, such as the conjunctiva, periarticular and kidney stones. It should be noted that serum albumin have impact on calcium concentration. Elevated serum calcium levels can be categorized into mild, moderate and severe.

- Mild hypercalcemia: total serum calcium values above the upper reference limit, but  $< 3\text{mmol/L}$ ;
- Moderate hypercalcemia: total serum calcium values  $3\text{-}3.5\text{mmol/L}$ ;
- Severe hypercalcemia: total serum calcium  $> 3.5\text{mmol/L}$ , while causing a series of serious clinical manifestations, namely hypercalcemia crisis.

The most common causes of hypercalcemia are primary hyperparathyroidism and malignant tumors, other reasons include: drugs: such as vitamin D, vitamin A, thiazide diuretics, lithium, theophylline, estrogen and anti-estrogen hormones; endocrine diseases, sarcoidosis and other granulomatous diseases, long-term immobilization, familial hypocalcinuric hypercalcemia and milk alkali syndrome. Once the patient's serum calcium is high:

- Confirm the existence of hypercalcemia, measure of serum calcium should be repeated to rule out laboratory error and prolonged tourniquet lashing or other human factors; be aware whether the patient is dehydrated or rise of plasma protein concentration.

- Once hypercalcemia is confirmed, the cause should be identified: researchers can determine whether to simultaneously monitor PTH, 25(OH)D, renal function, urinary calcium/creatinine clearance rate and alkaline phosphatase based on the patient's condition, and seek for other possible causes; if the patient is in the vitamin D3 treatment group, vitamin D3 therapy should be suspended.

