## **8.7 Treatment on vitamin D intoxication**

Vitamin D intoxication has no particular manifestation, similar to hypercalcemia. Early phase of acute intoxication first presents with increased serum 25-OHD and calcium, change of epiphysis appearing later. Abnormal X-rays can assist diagnosis, but negative results cannot rule out the possibility of vitamin D intoxication.

In the “Application Guideline for Vitamin D and Bone Health in Adult Chinese”, it refers American guideline that it is considered as potential vitamin D intoxication if 25(OH)D > 500nmol/L (200ng/ml) continuously. However, the actual incidence of vitamin D intoxication is low and it happens rarely in accidental overdose or inappropriate treatment with large dose.

In this study, the daily dose of vitamin D should be reduced to 800IU, if 25(OH)D>250nmol/L. When serum 25(OH)D>500nmol/L (200ng/mL), study should be suspended, withdrawal vitamin D and calcium, avoid sunlight, apply low calcium diet. Adrenal hormones can inhibit the intestinal absorption of calcium, and antagonize VitD. its impact on blood glucose should be noted.

When vitamin D intoxication meets the standards of serious adverse event, it should be reported as serious adverse event.

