## **3. Results reporting**

After receiving the samples, center laboratory will report the results of C-peptide and 25 (OH) D within a week, GADA results within 2 weeks.

Genetic testing result report is undetermined, currently after the completion of the study.

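### Scheduled 25(OH)D results that trigger vitamin D3 dose actions can take up to 21 days plus transit to reach the site, although the test is meant to detect excess promptly

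*Protocol*

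**What the plan says.** The protocol gives 25(OH)D a safety purpose. Section 1.3 (Benefit/risk and ethical assessment) introduces the monitoring with "To ensure the safety of the study and detect vitamin D3 excessive promptly". It also explains that the study dose of 2000 IU/day is above the 800 IU/day limit in the product specification, and that regular 25(OH)D measurement is needed for that reason.

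Two actions depend on the result, both in Section 8.7 (the first is also in Section 1.3):

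- At the lower limit, "the daily dose of vitamin D should be reduced to 800IU, if 25(OH)D>250nmol/L".
- Above 500 nmol/L, the rule is suspension, with vitamin D and calcium both stopped.

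Section 7.2.1 places the test centrally: "The sponsor will assign the central laboratory to carry out the safety assessment: test of 25(OH)D". The draws are at screening and weeks 4, 12, 26, 52, 78 and 104. Appendix C, in its list of test items, also puts 25(OH)D under the central laboratory.

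Appendix C then fixes the timing. Part 2 (Transportation) says "Deliver samples using dry ice to center laboratory every 14 days" and refers to separate transport operating instructions. Part 3 (Results reporting) says that, after receipt, "center laboratory will report the results of C-peptide and 25 (OH) D within a week". The text shown contains no alert for a value above 250 or 500 nmol/L, no urgent shipment and no local 25(OH)D test.

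**The concern.** A test whose result is meant to change or stop a study drug travels on the same schedule as C-peptide, an efficacy measure on which no dose action depends. Appendix C separates the central assays only by reporting time, with GADA slower, and not by whether the result calls for action. Followed as written, the logistics work against the stated purpose of the test.

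At stake is how long a subject in the vitamin D3 arm stays on 2000 IU/day after giving a sample that already meets one of the protocol's own limits. The concern is subject protection; the analysis of the primary endpoint is not affected. It applies chiefly to the draws at weeks 4, 12, 26, 52 and 78. The screening draw comes before vitamin D3 starts, and no study drug is dispensed at week 104.

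**Working it through.** The protocol states no total turnaround, so there is no figure of its own to reproduce. The delay is a direct sum.

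**Inputs**

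- Wait for shipment: 0 to 14 days (Appendix C, part 2).
- Laboratory time from receipt to report: up to 7 days (Appendix C, part 3).
- Transit: not given; taken as 0, with a range of 1 to 3 days as an assumption.
- Dose while the result is pending: 5 x 400 = 2000 IU/day (Section 5.2).
- Dose under the >250 nmol/L rule: 800 IU/day (Sections 1.3 and 8.7).
- Dose under the >500 nmol/L rule: vitamin D withdrawn, so 0 IU/day (Section 8.7).

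**Delay from draw to report** = shipment wait + transit + laboratory time.

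- Upper bound, no transit: 14 + 0 + 7 = 21 days.
- Upper bound with 1 to 3 days' transit: 22 to 24 days.
- Average, if draw dates fall evenly in the shipping cycle (mean wait 14 / 2 = 7 days) and there is no transit: 7 + 7 = 14 days if the laboratory uses its full week; 7 + 3.5 = 10.5 days if reports are spread evenly over the week.
- Share of samples taking 14 days or more, no transit: about 50% with the full laboratory week, about 25% with reports spread over it.
- Share taking 21 days or more, assuming 2 days' transit: the full laboratory week requires a shipment wait of at least 21 - 2 - 7 = 12 days, so (14 - 12) / 14 = about 14%; with reports spread over the week, about 2%.

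The time from report to contact with the subject comes on top, and the protocol gives no figure for it.

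**Dose taken beyond the protocol's own rule while the result is pending**

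| Delay | Above 250: days x (2000 - 800) | Above 500: days x 2000 |
|---|---|---|
| 10.5 days | 12,600 IU | 21,000 IU |
| 14 days | 16,800 IU | 28,000 IU |
| 21 days | 25,200 IU | 42,000 IU |

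The two limits must be kept apart, because the lower one reduces the dose and does not stop it.

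**Effect of a same-day laboratory alert.** It removes the time between measurement and report, at most 7 days. The shipment wait of up to 14 days, plus transit, remains.

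**The case against.** Four arguments on the other side carry weight.

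**Calcium is a faster safeguard.** Serum calcium and 24-hour urinary calcium and phosphate are tested at the sites at the same visits. Section 8.6 suspends vitamin D3 once hypercalcaemia is confirmed, without waiting for 25(OH)D. This stands and lessens the risk. It does not replace the 25(OH)D limits, because Section 1.3 itself says no clear relation is established between the upper safe 25(OH)D level and hypercalcaemia. A subject with normal calcium and a value above a limit is still caught only by the slow route.

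**The lag is small beside the sampling gaps.** Successive draws on treatment are 8 to 26 weeks apart, Section 1.3 describes 25(OH)D as slow to reach steady state, and potential intoxication is described there as a persistent level. The word promptly can also be read as referring to the sampling schedule. This limits the importance of the point. But the sampling gap determines when an excess is first measured; the lag follows a sample that already meets a limit, and adds to that gap.

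**Intoxication is expected to be rare.** Sections 1.3 and 8.7 say so. That lowers the expected harm, and also means that alerts would be few.

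**The transport instructions are not shown.** They may contain an urgent route. This stands as a limit on the finding.

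A reader might go further in three ways that the documents do not support.

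- That the 25(OH)D rules cannot act until weeks after the draw, or that a three-week lag follows every draw. Twenty-one days is the longest delay before transit; a sample drawn just before dispatch can be reported within days.
- That action must wait for the next scheduled contact, which is 4 weeks after each of the draws at weeks 4 to 78. Section 6.1 allows unscheduled visits for safety, and nothing ties the action to a scheduled one.
- That a subject with hypercalcaemia stays on full dose while a diagnostic 25(OH)D waits in the batch. Section 8.6 leaves that work-up to the site ("researchers can determine whether to simultaneously monitor PTH, 25(OH)D"), does not say that an unscheduled sample joins the batch, and already suspends vitamin D3.

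**Conclusion.** The point holds in a limited form. As written, Appendix C lets a scheduled 25(OH)D value that meets one of the protocol's own limits remain unknown to the site for up to 21 days before transit, and for about 10.5 to 14 days on average. That does not fit the stated aim of prompt detection, and the passages must be reconciled. At the upper bound, a subject with normal calcium takes 25,200 IU beyond the >250 nmol/L rule or 42,000 IU beyond the >500 nmol/L rule.

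The averages assume draws spread evenly over the shipping cycle and no transit time. Any figure above 21 days rests on an assumed transit time. The conclusion also assumes that the transport instructions hold no urgent route; if they do, what remains is a missing cross-reference. This is a gap in safety logistics that is worth closing. It is not evidence that subjects are left unprotected, and no view is taken on the dose or on either threshold.

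**What to change.** Reconcile Appendix C, parts 2 and 3, with Sections 1.3 and 8.7:

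1. State in Appendix C that the central laboratory notifies the site, on the day of measurement, of any 25(OH)D above the existing 250 or 500 nmol/L limits.
2. Confirm that the 14-day shipping interval for 25(OH)D fits the stated purpose of prompt detection, or, if the transport instructions already provide an urgent route, cite it in Appendix C.

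The first step removes only the reporting part of the delay, up to 7 days. The remaining wait of up to 14 days is why the second step is needed. The cost is a few lines in Appendix C and a small number of laboratory alerts. No dose, threshold or clinical rule is changed.

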## **3. Results reporting**

After receiving the samples, center laboratory will report the results of C-peptide and 25 (OH) D within a week, GADA results within 2 weeks.

Genetic testing result report is undetermined, currently after the completion of the study.

